### Dissemination plans {31a}

The study has been pre-registered on the National Institutes of Health U.S. National Library of Medicine ClinicalTrials.gov, identifier ID: NCT05611788. The research group also plans to present the study’s core findings to the stakeholders and the public through international peer-reviewed articles and conferences. Findings will also be shared with our participants upon their request with identifiable details being masked.

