**Trial registration:**

National Institutes of Health U.S. National Library of Medicine ClinicalTrials.gov NCT05611788. Registered on 7 November 2022. Protocol version: 11 May 2023.

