#### Secondary neuroimaging outcomes

All structural and functional scans are acquired on a 3 T Siemens MAGNETOM Prisma MRI scanner (Siemens Medical Systems, Erlangen, Germany) with a 64-channel head coil. MRI scans were conducted at two timepoints, namely pre-test and post-test for all participants. The same scan sequence is used for all pre-test and post-test MRI scans within each participant. However, there can be changes in scan sequence between participants due to technical issues.(1) Resting-state functional MRI datars-fMRI can reveal functional connectivity within and across brain networks that subserve task performance. A 10-min run of rs-fMRI data is acquired at both pre-test and post-test to investigate functional brain network changes that may result from the Structure Learning training. Before the rs-fMRI scan, participants are instructed to relax, fixate at a white cross presented at the centre of the screen, and to let their mind wander and not think about anything in particular. rs-fMRI images are acquired using Gradient Echo type Echo Planar Imaging (GRE-EPI) sequence with the following parameters: repetition time (TR) = 1280 ms; echo time (TE) = 30 ms; flip angle = 74^◦^; resolution matrix = 220 × 110 × 64; field of view (FOV) = 220 mm; thickness = 2.0 mm; acquisition voxel size = 2 × 2 × 2 mm^3^ resolution; integrated Parallel Acquisition Techniques = 4. A total of 64 slices are used to cover the whole brain including the cerebellum. Each 10-min run results in 462 volumes. In addition, high-resolution T1-weighted structure images are acquired using a Magnetisation Prepared Rapid Acquisition Gradient echo (MPRAGE) sequence with the following parameters: TR = 2000 ms; TE = 2.26 ms; inversion time = 800 ms; flip angle = 8°; FOV = 256 × 256; slices = 176; thickness = 1.0 mm; voxel size = 1 × 1 × 1 mm^3^).(2) Multi-parameter mappingMPM allows us to investigate different aspects of microstructural changes in grey matter and white matter. Recent evidence suggests that myelination is associated with behavioural plasticity in learning [41]. Hence, we focus on MPM parameters sensitive to myelin content, such as R1 and MT. All MPM scans are acquired with a 64-channel radio-frequency (RF) receive head coil and RF body coil for transmission. We use a multi-centre validated MPM protocol [48] in the present study. Three different multi-echo FLASH scans will be acquired with predominant T1-, PD-, and MT-weighting with appropriate choice of the TR and the flip angle. Multiple gradient echoes are acquired with alternating readout polarity at eight equidistant TE between 2.46 and 19.68 ms for the T1w, MTw, and PDw acquisitions. Acquisition parameters for T1-weighting and PD-weighting are as follows: voxel size = 1 × 1 × 1 mm^3^; slices = 176; FOV = 256; resolution matrix = 256 × 256; parallel imaging using GRAPPA factor in the phase-encoding (PE) direction = 2; 6/8 partial Fourier in partition direction, non-selective RF excitation, readout bandwidth BW = 480 Hz/pixel, RF spoiling phase increment = 50°. MT-weighting is achieved by applying an off-resonance Gaussian-shaped RF pulse (4 ms duration, 220° nominal flip angle, 2 k Hz frequency off set from water resonance) prior to the excitation. A pair of RF sensitivity maps are collected before each FLASH scans with the following parameters: 4 mm isotropic resolution, matrix = 256 × 64 × 48, parallel imaging using GRAPPA factor 2 in phase-encoding direction. The total acquisition time is around 15 min. The data-driven approach, i.e. unified segmentation-based correction of R1 maps for RF transmit inhomogeneities (UNICORT), is used to estimate B1 transmit bias field map [49].(3) Magnetic resonance spectroscopyMRS allows for non-invasive in vivo quantification of brain neurometabolites. In the present experiment, we targeted the measurement of the inhibitory neurotransmitter, GABA, in bilateral dorsolateral prefrontal cortex (DLPFC). Prior to all MRS scans, a high-resolution T1-weighted structural scan along the sagittal plane (MPRAGE; TR = 2000 ms; TE = 22.6 ms; TI = 800 ms; flip angle = 8°; FOV = 256 × 256; slices = 176; voxel size = 1 × 1 × 1 mm^3^) is acquired. We then 3D-reconstruct the axial and coronal planes and use images from all three planes to guide our voxel positioning on the DLPFC. We try to achieve consistent MRS voxel placement between subjects and sessions with the use of salient anatomical landmarks such as the dorsal anterior cingulate cortex, superior frontal gyrus, and middle frontal gyrus. In addition, we also try to maximise the sampling of grey matter in each region during voxel placement. After voxel placement, we ensure a homogeneous B_0_magnetic field within the DLPFC voxel with a two-step process. An automated B0 map-based shimming is first used to correct for shifts in linear gradients in the field. Subsequently, an interactive manual shimming procedure is used to correct for residual high-order heterogeneities in the B0 magnetic field. We aim to obtain an eventual shim that is as close to 16 Hz or preferably less than 16 Hz (full-width at half-maximum; FWHM) spectral linewidth. We then measured GABA levels with the widely used technique known as Mescher-Garwood Point Resolved Spectroscopy (MEGA-PRESS) [50, 51]. MEGA-PRESS implements J-difference editing to derive an edited signal that we then use it to quantify GABA levels. Two single voxel edited MR spectra are acquired from a 30 × 15 × 30 mm^3^ (in the *x*, *y*, and *z* dimensions) voxel of interest positioned separately in the left and right DLPFC. Two interleaved datasets are acquired within a single acquisition namely: (1) an edited ‘On’ inversion pulse at 1.98 ppm and (2) an ‘Off’ inversion pulse elsewhere at 7.5 ppm. Additional MEGA-PRESS parameters used are as follows: TR = 2000 ms; TE = 68 ms; spectral bandwidth = 1850 Hz; data points = 2048; readout duration = 1107 ms. We also acquire unsuppressed water spectra as a separate scan to allow for concentration reference to the water tissue. In total, 128 spectral averages (128 ‘On’ and 128 ‘Off’ pulses) are acquired during the metabolite scan and 4 spectral averages are acquired during the water scan resulting in a total scan duration of around 9 min.

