## Assignment of interventions: Blinding

### Who will be blinded {17a}

The study adopts a single-blind design with participants blinded to the full details of the Structure Learning training programme under investigation. Participants are informed that they are either in Group A or B without any knowledge of whether that refers to the Training or Control group. Training participants, i.e. participants in Group A, will complete the appropriate Structure Learning stage during each training session without knowledge of the stage progression criterion and the context-target stimuli contingency. Participants are only told to predict the next symbol as accurately as possible based on previously appearing ones. This is especially crucial for the study as it investigates whether cognitive flexibility can be improved via implicit learning from Structure Learning training. Control participants, i.e. participants in Group B, are unaware of the Structure Learning training programme. During the pre- and post-cognitive sessions, the construct measured by each task is non-explicit and never mentioned in the instructions given to the participants (e.g. ‘WCST is a card-sorting task’). This is to prevent task expectations from affecting participants’ performance. The group information is not blinded for experimenters during the administration of tests and data collections. However, manuals to standardise experimenters’ interactions with and instructions to the participants are prepared and intensive training provided for all experimenters to ensure consistency in all administered procedures. Researchers performing the data analysis will not be blinded to the group assignments. However, researchers’ biases are prevented during data analyses by setting hypotheses in advance with sufficient sample size planned prior to data collection. All final analysis scripts will be shared on open science platforms or repositories. Due to ethical regulations, the full data set will not be made available publicly. However, regulated data access can be provided to other researchers under request.

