## Trial status

Study recruitment began in May 2022 and data collection formally started in June 2022. The research team experienced multiple technical difficulties in the implementation of the planned scan sequences between July 2022 and October 2022. Data collection was paused and study protocol revised to resolve these issues. First registration of the revised version of the study protocol on ClinicalTrials.gov was completed on 7th November 2022. The current version of the study protocol will be in use until the end of our data collection projected to be in June 2023.

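### The study is called pre-registered, but by its own dates it was first registered on 7 November 2022, after data collection began in June 2022 and after a protocol revision

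*Protocol article*

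**What the plan says.** Dissemination plans {31a} states: "The study has been pre-registered on the National Institutes of Health U.S. National Library of Medicine ClinicalTrials.gov". The abstract, under Trial registration, reads "Registered on 7 November 2022". Trial status gives the chronology: "Study recruitment began in May 2022 and data collection formally started in June 2022". It then reports "multiple technical difficulties in the implementation of the planned scan sequences between July 2022 and October 2022" and continues: "Data collection was paused and study protocol revised to resolve these issues". The first registration of the revised version is dated there to 7 November 2022, with data collection projected to end in June 2023.

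Two other statements bear on the point. Who will be blinded {17a} leaves the analysts aware of group and says that "biases are prevented during data analyses by setting hypotheses in advance with sufficient sample size planned prior to data collection". Secondary neuroimaging outcomes says that one sequence is used for both scans of a given participant, but that "there can be changes in scan sequence between participants due to technical issues".

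**The concern.** Pre-registration means that a public, dated record existed before the data did. The article claims this, and its own dates contradict it. The label matters more than usual here. Analysts are not blinded, the primary outcomes cover four constructs measured by many tasks, and the stated protection against analytic bias is that hypotheses were fixed beforehand. A reader of the dissemination section would take the registration as independent evidence of that. For participants studied before November 2022 it cannot be.

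The second part concerns the scans. The protocol was revised because of scan-sequence problems, and sequences are allowed to differ between participants, yet the planned imaging analyses contain no term for sequence. Differences between sequences could then enter the correlations between brain change and training performance.

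**Working it through.** **Dates.** The inputs are the registration date (abstract and Trial status) and the start months (Trial status). Days within the months are not given, so each interval is a range.

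- Data collection to registration: 1 June to 7 November 2022 = 29 + 31 + 31 + 30 + 31 + 7 = 159 days. 30 June to 7 November = 31 + 31 + 30 + 31 + 7 = 130 days. Divided by 30.4375, this is 5.2 and 4.3 months.
- Recruitment to registration: 1 May gives 190 days and 31 May gives 160 days, or 6.2 and 5.3 months.
- Share of the projected June 2022 to June 2023 window elapsed at registration: 130/365 = 36% to 159/365 = 44%. This includes a pause of unstated length, so it does not measure the share enrolled.

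No choice of day within May or June puts registration first.

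**Were people studied before registration?** Trial status says that data collection had started. The section on auditing {23} describes an ethics-board check on 22 July 2022 at which consent forms had to be shown, which supports participants having consented by then. Table 3 puts the pre-test MRI in weeks 4–5 and the post-test MRI in weeks 8–9. For a June 2022 starter who was not paused, these fall between 22 June and 4 August and between 20 July and 1 September 2022. The post-test scan would then lie inside the July to October period of scan problems.

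**How many?** The article gives no count. Purely as an assumption, one, two or three full batches of 18 (Trial design {8}) against 120 planned (60 per group, Sample size {14}) would be 18/120 = 15%, 36/120 = 30% or 54/120 = 45%. The pause could make the true figure smaller, and the conclusion does not depend on it.

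**What sequence differences can do.** Suppose the measured value for a participant scanned with sequence s is Y = a_s + b_s·θ + e, where θ is the true quantity and e has variance σ_s². With the same sequence at both visits, and errors independent between visits:

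Y_post − Y_pre = b_s·(θ_post − θ_pre) + (e_post − e_pre), with error variance 2σ_s².

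The offset a_s cancels. The scale b_s and the noise σ_s do not, so both can still affect a correlation across participants between change and training performance. That correlation is the planned analysis for connectivity, GABA+ and MPM. In addition, the group independent component analysis takes scans from both groups and both sessions together, and the MPM values are read from masks derived from it. Mixed sequences could therefore influence the components before any difference is taken. None of the three analysis sections names a sequence term.

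**The case against.** The chronology is not hidden: the correct dates stand in the abstract and in Trial status, so the error could be seen as a single word. That is fair as to intent, but the word still claims a property that the study lacks.

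The phrase about first registration of the revised version might suggest that an earlier version had been registered before. The article gives one registry number and one registration date and mentions no other, so this reading has no support.

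The safeguard in {17a} is that hypotheses were set in advance, not that they were registered, and the section on amendments {25} describes protocol versions and approval letters kept on file. This stands: hypotheses may well have been fixed in time. The registration simply cannot be the evidence for it.

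On imaging, the same sequence within each participant and the post-minus-pre scores are real protection, and they remove any constant offset. Interim analyses {21b} and the missing-data section {20c} also provide for quality checks, a log of deviations and the discarding of unusable scans. These deal with faulty data. They do not deal with usable data acquired under a different sequence.

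A reader might infer more: that two protocol versions are pooled in one analysis population, that early data shaped the revision, or that the primary comparison is compromised. The documents do not support these.

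- **Pooling** is nowhere stated. The article does not say whether the early participants were kept, rescanned or dropped.
- **The revision** has only a technical reason given. No change to eligibility, training, behavioural tasks or hypotheses is described.
- **The primary outcomes** are behavioural, and Sequence generation {16a} does not allow two successive participants in the same group. Both groups therefore fill at nearly the same rate, and protocol version should not be confounded with group.

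**Conclusion.** The concern holds in limited form. The pre-registration claim is wrong on the article's own dates: registration followed the start of data collection by 130 to 159 days and came after a protocol revision. For participants studied before 7 November 2022, registration does not document that hypotheses preceded data. Their number and their place in the analysis are not stated, so no share of the sample can be asserted.

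The imaging part is a modest weakness. Between-participant differences in sequence are allowed and not modelled. Offsets cancel in the change scores, while scaling, noise and effects on the pooled component analysis may remain. The size cannot be computed, because the article does not say how the sequences differed or how many participants had each.

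This is not evidence of outcome switching, and it does not show bias in the primary behavioural comparison.

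**What to change.** 1. In Dissemination plans {31a}, replace the pre-registration claim with a statement that the study was registered on 7 November 2022, after data collection began in June 2022. Cost: one sentence, and a less favourable description.
2. Report how many participants were enrolled before that date and whether they are included in the analysis. Cost: one count and one statement.
3. Record the scan-sequence version for each participant. In the connectivity, GABA+ and MPM change analyses, include it as a covariate (a partial correlation or regression in place of the simple correlation), or repeat the analyses in participants scanned with the current sequence. The covariate keeps everyone but adjusts only for average differences between sequences. The restricted analysis, with the component analysis rerun, also deals with scaling, noise and the components themselves, at the price of fewer participants.

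Repeating the primary behavioural comparison in later participants is optional. No problem shown in the documents requires it.

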## Discussion

This paper outlines the protocol for conducting a Structure Learning training programme and the evaluation of its effectiveness with regard to various cognitive domains. Participants are matched based on age, sex, intelligence, and cognitive performances in a Baseline Cognitive Session and assigned equally into either a Control or Training group. Both groups will then be required to complete a pre-training cognitive assessment that comprises of standardised tests that measure intelligence, and language and numeracy skills. Following that, participants undergo the pre-training MRI scans. During a period of 2 weeks, the Training group commences on their Structure Learning training sessions, whereas the Control group will not be given any form of training. Post-training MRI scans will be taken immediately after the end of the 2-week gap. Finally, two post-training cognitive sessions will be conducted for both groups of participants.

As this study is conducted in a single-blind manner, participants are not privy to the group they are assigned to, while experimenters are aware of the group participants are in. This may result in an increased likelihood of experimenter bias, where the experimenter may unknowingly provide certain cues or lead participants in a certain way during Structure Learning training sessions or cognitive sessions. Additionally, there are certain cognitive assessment that requires a slightly level of subjective judgement in scoring participant responses; preconceived notion about the group assigned to the participant may cause experimenters to have slight differences when scoring these responses.

The Structure Learning training outlined in this study is designed to target improvements in CF, as well as potential transfers to other cognitive functions. As highlighted earlier in this paper, cognitive flexibility is an important cognitive function, contributing to better adaptability in dynamic changes in environment [70] and other important activities of daily living. The development of a training will be critical with higher attentions to improve cognitive capabilities across the ages. Additionally, the correlating of behavioural training outcomes to neurological model can also contribute to better understanding of neuropsychological model of learning. This paper will also serve as a basis of reference to assist other researchers in designing their study.

## Trial status

Study recruitment began in May 2022 and data collection formally started in June 2022. The research team experienced multiple technical difficulties in the implementation of the planned scan sequences between July 2022 and October 2022. Data collection was paused and study protocol revised to resolve these issues. First registration of the revised version of the study protocol on ClinicalTrials.gov was completed on 7th November 2022. The current version of the study protocol will be in use until the end of our data collection projected to be in June 2023.

## Data Availability

Any data required to support the protocol are available from the authors upon reasonable request and with the permission of both NRF and NTU.

## Abbreviations

CF: Cognitive flexibility
CLIC: Centre for Lifelong Learning and Individualised Cognition
DLPFC: Dorsolateral prefrontal cortex
EF: Executive function
EPI: Echoplanar imaging
FOV: Field of view
FWHM: Full-width at half-maximum
GABA: γ-Aminobutyric acid
GICA: Group independent component analysis
Glx: Glu + glutamine
GM: Grey matter
ICD: Integral curve difference
IRB: Institutional review board
MPM: Multi-parameter mapping
MRS: Magnetic resonance spectroscopy
NTU: Nanyang Technological University
PI: Performance index
R_2_: Transverse relaxation rate
RF: Radio-frequency
rs-fMRI: Resting-state functional MRI
SNR: Signal-to-noise ratio
tCho: Choline
tCre: Creatine
TE: Echo time
TI: Inversion time
TR: Repetition time
VBQ: Voxel-based quantification
WM: White matter
